**Study aim**

The present study aims to evaluate the difference in clinical outcome and satisfaction between conventional sedation with meperidine/propofol and pain focused sedation with fentanyl/propofol for ERCP.

**Background**

Adequate sedation is an essential factor of ERCP in order to reduce patient discomfort and enhance performance of the endoscopist. (1) Propofol is widely used for sedation during ERCP due to its fast onset, short half-life and rapid recovery. One of the most commonly used regimen for sedation is meperidine/propofol, which gives meperidine before the procedure for analgesia and uses propofol for sedation during the procedure. However, using propofol alone during the procedure has the downfall of possible oversedation, apnea and desaturation due to its narrow therapeutic window. Moreover, a single dose of meperidine before the procedure is often insufficient for adequate analgesia during the whole procedure, leading to an increase in propofol dose in order to overcome this problem with deeper sedation. In an attempt to supplement the lack of analgesic properties of propofol, we added fentanyl to propofol infusion during sedation for ERCP, and aim to compare this regimen with the conventional method with regard to quality of sedation and clinical outcomes in the present study.

**Sample size calculation**

Based on a previous study that compared sedation methods for ERCP (2), 100 patients are needed in each group in order to detect a 20% difference in recovery time between the two groups at a significance level of 0.05 and 85% power (α=0.05, 1-β(power)=0.85) considering a type I error of 0.05.

**Inclusion criteria**

Adult patients older than 19 years scheduled for ERCP under sedation

**Exclusion criteria**

1. Patients with known allergies to eggs, soybeans of sulfites

2. ASA class V

3. Pregnant of breastfeeding patients

4. Patients with hemodynamic instabilities that are considered unfit for ERCP under sedation.

5. Patient refusal and those unable to provide informed consent

**Institution and study period**

Institution: Yonsei University College of Medicine, Severance Hospital

Study period: 12 months following approval of IRB

**Screening**

1. Height, weight, history of smoking and alcohol intake, history of snoring, any symptoms of upper respiratory infection within 2 weeks

2. Initial visit, primary symptoms, duration of symptoms, ECOG performance status

3. Vital signs (blood pressure, pulse rate, temperature, respiratory rate)

4. Physical examination: Determine status of general appearance, skin, ears-nose-throat, eyes, cardiovascular system, chest/lungs, abdomen, musculoskeletal, neurological status

5. Underlying diseases

6. Family history of malignancies

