**Study end point**

1. Primary end point
   1. Recovery time (time from scope withdrawal to full recovery)
   2. Adverse event during and after procedure
      1. Desaturation (SaO2 < 90% for > 10 sec, need for jaw thrust) rate
      2. Apnea (cessation of respiratory activity for > 30 sec under visual observation)
2. Secondary end point
   1. Overall satisfaction with sedation and procedure by endoscopist (VAS, 0 ~ 100)
   2. Overall satisfaction with sedation by patients (VAS, 0 ~ 100)

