**Statistical analysis**

Continuous variables will be analyzed with either the independent two sample t-test or the Mann-Whitney U Test depending on distribution. Categorical variables will be analyzed by the Chi-square or Fisher’s exact test. A P value of < 0.05 is defined as statistically significant.

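### The stated test for the desaturation and apnea primaries is unadjusted although snoring, height and weight are collected: an optional gain of about 0 to 5 power points

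*Protocol*

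**What the plan says.** The Protocol's Screening section lists, as its first item, "Height, weight, history of smoking and alcohol intake, history of snoring, any symptoms of upper respiratory infection within 2 weeks". BMI is not named but follows from height and weight.

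The Study end point section puts "Adverse event during and after procedure" among the primary end points, beside recovery time, with two components: "Desaturation (SaO2 < 90% for > 10 sec, need for jaw thrust) rate" and "Apnea (cessation of respiratory activity for > 30 sec under visual observation" (the bracket closes there in the Protocol).

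The Statistical analysis section is three generic sentences. The one that reaches these two end points is "Categorical variables will be analyzed by the Chi-square or Fisher’s exact test". It names no covariate and no adjusted model. Study design and method describes randomisation from computer-generated random numbers and names no stratification factor.

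The sample size section sets 100 per group, with alpha 0.05 and power 85%, and ties that size to one end point only: "in order to detect a 20% difference in recovery time between the two groups". It gives no standard deviation, and it gives no rate for desaturation or apnea.

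**The concern.** Desaturation and apnea carry primary status, but the trial was sized on recovery time alone, so their power is whatever 200 patients happen to give. Snoring and body size are plausible predictors of airway events and are on file before treatment. If they do predict these events, a crude two-by-two comparison leaves that variation in the error, and neither the design nor the stated analysis uses it.

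Chance imbalance is a related, modest matter. With 30% to 40% snorers (assumed) and simple randomisation of 100 per arm, there is a 14% to 17% chance that the arms differ by 10 or more percentage points in snorers. With 40% snorers, a snoring odds ratio of 2 to 4 and an overall event rate of 10% to 25%, a 10-point imbalance moves the crude risk difference by about 0.6 to 2.6 points. Pre-specified adjustment removes this in expectation, and it prevents covariates from being chosen after an imbalance has been seen.

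What is at stake is a little power at no extra recruitment. The validity of the trial is not in question.

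**Working it through.** **Inputs.** From the Protocol: 100 per group, alpha 0.05 (taken as two-sided, since the side is not stated), power 85%, a 20% difference in recovery time, and chi-square or Fisher for categorical variables. Assumed: each airway end point is analysed as patients with at least one event; event rates, covariate frequencies and odds ratios (OR) are varied over a range.

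**1. The plan's own figure.** For two means, n per group = 2 × [(1.960 + 1.036) × SD / difference]². With n = 100, the standardised difference is 2.996 × √(2/100) = 0.424. A 20% difference therefore implies an SD of 0.20 / 0.424 = 47% of mean recovery time. An SD of 40% gives n = 72, 47% gives 100 and 50% gives 113. The figure is plausible but cannot be verified without the SD, and it says nothing about desaturation or apnea.

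**2. Crude power for the airway end points at 100 per arm.** Power = Φ{[|p1 − p2| − 1.96 × √(2p̄(1 − p̄)/n)] / √([p1(1 − p1) + p2(1 − p2)]/n)}. For 20% vs 10%, p̄ = 0.15, the null SE is √(2 × 0.15 × 0.85/100) = 0.0505 and the alternative SE is √((0.16 + 0.09)/100) = 0.0500. So z = (0.1000 − 0.0990)/0.0500 = 0.02, and power is 50.8%.

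**3. Large-sample gain from adjustment.** Let f1 and f2 be the covariate-specific risks in each arm. The variance ratio is r = {E[f1(1 − f1)] + E[f2(1 − f2)] + ½Var(f1 − f2)} / {p1(1 − p1) + p2(1 − p2)}. Adjusted power is the formula in step 2 with n = 100/r. Assumed covariates: snoring 35%, recent respiratory infection 8%, standardised BMI. OR for snoring / infection / BMI per SD: weak 1.3/1.3/1.15, moderate 2/2/1.4, strong 3/3/1.8.

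| Rates | Crude | Weak | Moderate | Strong |
|---|---|---|---|---|
| 10% vs 5% | 26.7% | 26.8% | 27.2% | 28.2% |
| 15% vs 5% | 65.6% | 65.8% | 66.8% | 68.8% |
| 20% vs 10% | 50.8% | 51.0% | 52.2% | 54.7% |
| 30% vs 15% | 72.2% | 72.5% | 74.2% | 77.2% |

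The gain in effective sample size is 0.3% to 0.7% (weak), 2.1% to 4.6% (moderate) and 6.4% to 12.3% (strong). For example, strong covariates at 20% vs 10% give r = 0.909, and 100/0.909 = 110 per arm. This table uses three covariates, one more than the model proposed under the fix.

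**4. Simulation of the two-covariate model** (arm, snoring, BMI; score test against the crude chi-square; 40% snorers; 15,000 trials per setting; Monte Carlo standard error about √(0.81 × 0.19/15,000) = 0.3 points per estimate).

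| Rates | OR snoring / BMI per SD | Crude | Adjusted | Gain (points) |
|---|---|---|---|---|
| 25% vs 10% | 2 / 1.3 | 81.1% | 81.6% | 0.5 |
| 25% vs 10% | 3 / 1.5 | 81.9% | 83.8% | 1.9 |
| 25% vs 10% | 4 / 2 | 81.3% | 85.4% | 4.1 |
| 15% vs 5% | 3 / 1.5 | 68.6% | 69.4% | 0.8 |
| 15% vs 5% | 4 / 2 | 68.7% | 71.5% | 2.8 |

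With weak or non-prognostic covariates the score test gains about 0 points.

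**5. Type I error.** In the simulation of step 4 it was 5.1% crude and 5.3% adjusted. Over a wider set of null settings the score test stayed at about 4.4% to 5.5%. The likelihood-ratio test drifted above nominal, up to about 6% to 7%, when events were few (5% in both arms, about 10 events in total). That is the reason to name the score test.

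**6. Event counts.** Expected totals at 100 per arm are 10 + 5 = 15, 15 + 5 = 20, 20 + 10 = 30, 25 + 10 = 35 and 30 + 15 = 45. The model has three coefficients besides the intercept. Ten events give 10/3 = 3.3 per coefficient, and 20 give 20/3 = 6.7. With a threshold near 20, a trial at 10% vs 5% would usually use the crude test, and one at 15% vs 5% would sit on the boundary. The gains in those rows would then be lost wholly or in part.

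**The case against.** The case for leaving the plan alone is strong, and most of it stands.

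- **The crude test is valid.** A reader might infer that leaving chance imbalance uncorrected biases the comparison. It does not: the type I error of a randomised crude comparison already allows for chance imbalance.
- **Covariates are commonly left to the SAP, which is not at hand.** The Statistical analysis section is generic and excludes nothing, so one cannot say that the plan forbids an adjusted analysis. What remains is that the Protocol is not silent on the test. It names an unadjusted one for a class of variables that includes two primaries, and that stated choice can be improved.
- **The prognostic link is not in the document.** The Protocol never calls the screening items airway risk factors. The same list covers a general work-up down to family history of malignancies, and weight is needed for dosing per kg. That snoring and BMI predict these events is an assumption, and with weak prognosis the gain is near zero.
- **Adjustment does not rescue these end points.** A reader might conclude that substantial power is being forfeited, or that adjustment makes the airway primaries adequately powered. The tables support neither. Nor can it be said that these end points are certainly underpowered: crude power is about 81% to 82% at 25% vs 10% and 27% at 10% vs 5%, and the Protocol does not say which is nearer. Sizing on recovery time alone is a separate and larger question.
- **More covariates would be fragile.** Recent respiratory infection, smoking or a pre-sedation oximetry reading are tempting additions, but the event counts in step 6 do not support a longer model.

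**Conclusion.** The point holds as an optional improvement. The Protocol states an unadjusted chi-square or Fisher test for categorical variables, these include the desaturation and apnea primaries, and snoring, height and weight are already collected before treatment. Replacing the crude test with a small pre-specified model would add about 0 to 2 power points with weak or moderate covariates and up to about 5 with strong ones, at essentially unchanged type I error if the score test is used. The size rests wholly on assumed event rates, covariate frequencies and odds ratios, none of which the Protocol gives. Keeping the crude test would not be a fault.

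**What to change.** In the Statistical analysis section, add for desaturation and for apnea, each taken separately:

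- a logistic model with arm, snoring (yes/no) and BMI, with arm tested by the score test (not the likelihood-ratio test) at the two-sided 0.05 level;
- the standardised risk difference between arms with its 95% CI as the reported effect;
- the crude chi-square or Fisher test as a sensitivity analysis, becoming the primary test if the total number of events for that end point, counted blind to arm before unblinding, falls below a pre-set threshold. About 20 is reasonable for two covariates; this is a judgement and should be fixed in advance.

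No further covariates and no new data are needed. The cost is a few sentences and a slightly more complex analysis and report. If snoring and BMI turn out to be weakly prognostic, the return is little or nothing.

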**Standard diagnosis and therapy for studied disease**

Propofol based sedation with or without supplementary opioids is the most commonly used method for sedation during ERCP. However, there is no protocol that is accepted as standard sedation.

**Study design and method**

This study will be conducted on patients scheduled for elective ERCP at Yonsei University College of Medicine, Severance Hospital. The study period is 1 year after IRB approval. Patients will be randomized to either the control of study group until 100 patients are enrolled in each group. Randomization will be carried out by using a computer generated table of random numbers. The allocation sequence is sealed in an envelope and revealed only to the attending anesthetist providing sedation when the patient arrives at the endoscopic unit. The anesthetist will perform sedation according to the allocated group, and the patients, other study investigators and medical personnel will remain blinded to sedation method. If the targeted amount of patients are not recruited within 12 months, the study period will be extended.

Targeted level of sedation is MOAA/S (Modified Observer’s Assessment of Alertness/Sedation Scale) score 3 to 4 in all patients. Sedation in the Conventional Group is done by administrating 25 mg of IV meperidine (Pethidine, Jeil Pharmaceutical Co. Lt., Daegu, Korea) and 1 mg kg^1-^ of propofol (Pofol, Dong Kook Pharmaceutical Co. Ltd., Seoul, Korea) initially, followed by propofol infusion at a maintenance rate of 60 µg min^1-^ kg^1-^ using an automated pump (Terufusion® Syringe Pump TE-331, Terumo Corporation, Tokyo, Japan). Additional doses of 10 mg of propofol will be given when patients complain of discomfort/pain, or when the endoscopist demands deeper sedation. Patients of the Combination Group will be given 1 µg kg^-1^ of IV fentanyl (Hana pharmaceutical, Korea) and 0.4 mg kg^-1^ of propofol initially, followed by propofol infusion at a maintenance rate of 30 µg min^-1^ kg^-1^. Additional doses of 10 mg of propofol will be given during insufficient sedation, while bolus doses of 0.5 µg kg^-1^ of fentanyl will be given when additional analgesia is needed as judged by the anesthetist.

Patients will be monitored for blood pressure, pulse rate and pulse oximetry every 5 minutes throughout the procedure. Any events of apnea (cessation of voluntary respiratory for more than 30 seconds), desaturation (SpO2 lower than 90% for more than 10 seconds requiring chin lift/jaw thrust), procedure interruption due to apnea and/or desaturation for ambu bagging or other airway management are noted. Total dose of sedatives and analgesics are recorded. After the procedure, the patients are moved to the sedation recovery unit and monitored for vital signs and recovery of consciousness until the Modified Aldrete Score is 10 points and the patient is fit for discharge to the general ward. When the patient is fully alert and stable, satisfaction scores are recorded in a numerical rating scale of 0 to 100 by a nurse that is blinded to sedation method. Endoscopists will give satisfaction scores at the end of procedure.

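### A primary safety outcome, desaturation, counts only if an airway manoeuvre was needed, with no criterion for need and no named blinded assessor, so its rate may partly reflect how readily staff intervene

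*Protocol*

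**What the plan says.** The Protocol defines desaturation twice. Under 'Study design and method', in the monitoring paragraph, the event is "desaturation (SpO2 lower than 90% for more than 10 seconds requiring chin lift/jaw thrust". Under 'Study end point', where it is listed as a primary end point, it is "Desaturation (SaO2 < 90% for > 10 sec, need for jaw thrust) rate". Both definitions join an oximetry threshold to an airway manoeuvre. They differ in two details: chin lift or jaw thrust against jaw thrust alone, and SpO2 against SaO2.

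On blinding, 'Study design and method' says that the allocation is "revealed only to the attending anesthetist providing sedation when the patient arrives at the endoscopic unit", and that "the patients, other study investigators and medical personnel will remain blinded to sedation method".

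On recording, the same section lists apnea, desaturation and procedure interruption as events to be noted, in the passive. It does not say who decides that a manoeuvre is needed, who performs it or who writes the event down. By contrast, it states that the nurse who records patient satisfaction is blinded to the sedation method.

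**The concern.** The oximetry part of the definition is objective. The manoeuvre part is a decision by someone in the room, and the protocol gives no rule for it. Two patients with the same saturation trace can be classified differently: the one who received a jaw thrust has an event, and the one whose saturation recovered unaided does not.

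If the threshold for intervening were the same in both arms, this would only narrow the outcome. But the person giving sedation knows the arm, and the two regimens differ visibly to that person. If awareness of the regimen changes how readily a manoeuvre is used, a primary safety outcome will differ between arms even when patients desaturate equally often. Analysis could not repair this, because episodes without a manoeuvre are not events under the definition and need never be recorded.

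**Working it through.** **What the documents establish**

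1. Desaturation is a primary end point ('Study end point').
2. A manoeuvre is a necessary part of the event (both definitions).
3. No criterion for needing a manoeuvre is given in either section.
4. The sedation provider is unblinded: the sequence is "revealed only to the attending anesthetist providing sedation".
5. No assessor, blinded or otherwise, is named for this event.

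It is not stated that the anesthetist judges the need for a manoeuvre. That is inferred from the role.

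**Can the mechanism matter at this sample size?**

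The protocol has no desaturation figure to reproduce; its sample size rests on recovery time. Only the 100 patients per group ('Sample size calculation') and the 0.05 threshold with a Chi-square or Fisher's exact test ('Statistical analysis') come from the document. The true desaturation rate and the manoeuvre proportions are assumptions.

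Let p be the true proportion of patients with SpO2 below 90% for more than 10 seconds, equal in both arms. Let m1 and m2 be the proportions of those episodes that are followed by a manoeuvre. The recorded rates are then

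- arm 1: p × m1
- arm 2: p × m2

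The false-positive rate is the probability that a two-sided uncorrected chi-square test gives P < 0.05. It was obtained by exact enumeration of two independent Binomial(100, rate) counts.

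With p = 20%:

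| Manoeuvre use | Recorded rates | False-positive rate |
|---|---|---|
| 100% vs 100% | 20% vs 20% | 5.1% |
| 95% vs 90% | 0.20 × 0.95 = 19% vs 0.20 × 0.90 = 18% | 5.5% |
| 90% vs 70% | 18% vs 14% | 12.2% |
| 90% vs 60% | 18% vs 12% | 22.3% |
| 90% vs 50% | 18% vs 10% | 37.6% |

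Sensitivity to the assumed true rate:

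| True rate p | 90% vs 70% | 90% vs 50% |
|---|---|---|
| 5% | 5.5% | 10.2% |
| 10% | 8.3% | 19.5% |
| 20% | 12.2% | 37.6% |
| 30% | 16.7% | 55.8% |

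When the manoeuvre condition is applied equally or removed, the test holds its level: 4.4% to 5.2% over true rates of 5% to 30%. A small imbalance in manoeuvre use is close to harmless. A gap of 20 percentage points or more is not, unless desaturation is rare.

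**The case against.** There is a good case for the present definition. The SpO2 threshold is objective, so only the added condition is discretionary. Requiring a manoeuvre restricts the count to episodes that needed action, which may be closer to what clinicians care about. The two regimens are given and titrated differently, so the sedation provider has to know the allocation. Recovery time, on which the trial is sized, is unaffected. The larger false-positive rates above need large differences in manoeuvre use, for which the documents offer no evidence. All of this stands, and it limits the weight of the point. It does not explain why the discretionary part has no criterion and no blinded assessor.

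Three stronger readings are not supported.

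- **The unblinded anesthetist makes and records the call.** The protocol never says so. Events and "procedure interruption due to apnea and/or desaturation for ambu bagging or other airway management are noted". Since other medical personnel are described as blinded, a blinded recorder is compatible with the text.
- **The oximetry schedule cannot detect the event.** The protocol does say "Patients will be monitored for blood pressure, pulse rate and pulse oximetry every 5 minutes throughout the procedure", and readings 5 minutes apart would miss most episodes of 10 seconds or so. But a separate sentence says that any events are noted. The schedule is better read as a charting interval than as the means of detection. Sparse capture that was equal across arms would also cost power rather than create a difference.
- **The same defect affects apnea.** Apnea is defined as "Apnea (cessation of respiratory activity for > 30 sec under visual observation", with no manoeuvre condition, so this mechanism does not carry over. It too lacks a named assessor.

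**Conclusion.** The concern holds in a limited form. As written, the primary desaturation rate depends partly on intervention behaviour, which has no stated criterion and which is presumably in the hands of the one person who knows the allocation. Differential ascertainment is therefore possible. Its size and direction cannot be derived from the documents, and nothing in them shows that it will occur. Under the assumed 20% true rate the consequence runs from negligible (5.5%) to serious (37.6%), depending wholly on the assumed gap in manoeuvre use.

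Separately, and without any assumption, the two definitions of the same primary outcome do not match and must be reconciled. The change is recommended rather than essential, and it is cheap.

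**What to change.** - In 'Study design and method' and 'Study end point', define the outcome in identical words as SpO2 below 90% for more than 10 seconds, whether or not an airway manoeuvre followed. This settles SpO2 against SaO2 for the outcome.
- Record every such episode. Where the oximeter keeps a trend or alarm log, use it, read without knowledge of allocation. The documents do not say that such a record exists; if it does not, have blinded staff already present note the episodes. Name who does this.
- Report airway manoeuvres as a separate outcome, with one consistent wording in place of chin lift/jaw thrust in one section and jaw thrust in the other. Keeping this outcome preserves the intervention-based rate for comparison with other studies.
- State that some performance bias remains: an early manoeuvre can still end an episode before 10 seconds, so the new definition reduces the problem without removing it.

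The cost is protocol wording, a few case report form fields and, where possible, storage of the oximeter record. Counts will rise because brief self-resolving episodes are included. How desaturation is managed clinically does not change.
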